In the highlands of Western Kenya, malaria transmission is also highly variable despite universal high coverage rates with insecticide treated nets (ITNs) and indoor residual spraying (IRS). In Rachuonyo district, community surveys that were conducted in 2010 indicated parasite prevalences averaging 14.8% but ranging from 0% to 51.5%. School surveys that were conducted in the same year at 46 schools in the district revealed an even more marked variation in children aged 8-14 years where parasite prevalence was on average 25.8% but ranged from 0 to 71.4%. These findings indicate that the current control efforts are insufficient to control or eliminate malaria in parts of the district. One of the reasons that may underlie this apparent failure to interrupt local malaria transmission may be the presence of outdoor biting and resting mosquitoes. Work conducted by the Malaria Transmission Consortium in Rachuonyo has recently indicated that a sizeable proportion of mosquitoes may feed outdoors in the Kenyan highlands [[name] *et al.*, in preparation]. Outdoor biting vectors may remain largely unaffected by control tools that target indoor biting and/or resting mosquitoes like IRS and ITNs. Additional malaria control efforts may therefore be needed in areas where transmission persists: control efforts that reduce malaria transmission regardless of the biting or resting behaviour of the mosquito vector. These targeted interventions are likely to have an impact on malaria transmission in the entire district since small areas with higher malaria transmission intensity form important contributors to overall malaria transmission. Households that are exposed to higher numbers of infected mosquito bites consequently have a higher parasite load in humans. This clustering results in an amplification of malaria transmission: households that are highly exposed to infected mosquitoes also form an important source of malaria infection for uninfected mosquitoes that can spread malaria in the rest of the community [[7-9](#_ENREF_7)]. Hotspots of malaria transmission can thereby increase the efficiency of malaria transmission by a factor 2 to 4 [7-8].

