## c. Definition of clusters for interventions

## The data collected during the intensive cross-sectional surveys (SSC 1802) will be used to detect hotspots of malaria transmission in the study area based on malaria parasite prevalence and antibody responses. Hotspots will be defined as areas that are smaller than 1km^2^ with a level of transmission intensity that exceeds that in the surrounding area (in all directions). This will be indicated by a statistically significant higher parasite prevalence in combination with a statistically significant higher SCR and/or age-adjusted density of antibodies malaria antigens.

Malaria parasite prevalence will be determined by PCR-based detection of parasites based on the *P. falciparum* mitochondrial cytochrome b gene [15].

Malaria specific antibody responses will be quantified as the age-dependent seroconversion rate (SCR) for antibodies against malaria: antigens apical membrane antigen-1 (AMA-1), merozoite surface protein-1 (MSP-1_19_) and glutamate-rich protein (GLURP) [[12](#_ENREF_12)]. Antibody responses will be measured by standard ELISA methodology [12, 16] and the SCR will be determined by fitting a simple model to the age-dependent prevalence of antibody responses, as described in detail in publicly available protocols [16]. In addition, age-adjusted antibody densities will be calculated [17]. The SCR will be estimated for geographical subsets of 50 observations.

Hotspots will be of variable size and no quantitative estimate of the elevated transmission intensity inside hotspots can be given a-priori since this depends on the transmission intensity of the surrounding area [2-3,16]. Clusters will include hotspots and a surrounding ‘evaluation zone’ of 500m from the edge of the hotspot (see figure 2); this forms the unit of randomization. The grid structure that divided the study area into 250x250m cells, created as part of the baseline cross-sectional study will be used as easy references for the areas defined as hotspots. The size of a hotspot or intervention area will not be defined by the maximum mosquito dispersal range. We are not aiming to identify independent niches of malaria transmission. Minimum distance between hotspots will be 1km. Mosquito dispersal outside hotspots of malaria transmission is essential for the community effect and forms the cornerstone of our evaluation.

[figure not shown]

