Our primary outcome of interest is the impact of hotspot-targeted interventions on parasite prevalence in the area surrounding the hotspot (the evaluation zone). If we evaluate our intervention in 300 randomly selected individuals living outside the hotspot per cluster and assume a conservative estimate of k (0.5 coefficient of variation of true proportions between clusters within each group), we need 8 clusters per arm to detect a reduction from 10% parasite prevalence at baseline to ≤ 5% after the intervention. The actual number of people sampled will depend on the size of the hotspot and surrounding evaluation zone, with a target of sampling 20% of the population in the evaluation zone (≤500m from edge hotspot) or a minimum of 100 and maximum of 500 people. The unit of randomization will be at the compound level therefore 100 people would equate to approximately 35 compounds.

We aim to evaluate the interventions in all age groups above 6 months. If the PCR results of the intensive survey indicates that parasite prevalence is below 10% in certain age groups, these age groups will be considered less suitable for evaluation purposes; they will receive the standard of care provided by the study, including screening and treatment of all febrile cases, but will not be routinely sampled.

To understand possible effect differences between clusters, we also want to determine whether our intervention succeeded in reducing malaria transmission inside hotspots. The estimated parasite prevalence in individuals between 6 months and 20 years of age who are living in hotspots is >20% ([name] *et al.*, unpublished data). With a sample size of 100 individuals per cluster (i.e. per hotspot in 16 clusters), we would be able to detect a reduction to ≤ 5% after the intervention (k=0.5; Z_α/2_=1.96; Z_β_=0.84). Again the actual number sampled will depend on the size of the hotspot, with a target of sampling 20% or a minimum of 50 individuals (approximately 9 compounds).

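### The sample size calls k = 0.5 conservative without a source; the protocol's own prevalence spreads make a larger k plausible, and 8 clusters per arm give only about 60% power outside hotspots even at 0.5

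*Protocol*

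**What the plan says.** Section 9e makes two calculations.

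- **Evaluation zone, the main outcome.** It takes "300 randomly selected individuals living outside the hotspot per cluster", asks the reader to "assume a conservative estimate of k (0.5 coefficient of variation of true proportions between clusters within each group", and concludes that "we need 8 clusters per arm to detect a reduction from 10% parasite prevalence at baseline to ≤ 5% after the intervention".
- **Hotspots.** "With a sample size of 100 individuals per cluster (i.e. per hotspot in 16 clusters", it claims to detect a fall from above 20% to 5%, with "k=0.5; Z_α/2_=1.96; Z_β_=0.84".

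No source, pilot estimate or sensitivity range is given for k. The significance level and power are printed only beside the hotspot calculation.

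Section 5 (repeated in 9b) reports two 2010 spreads. For 46 schools in the district, in children aged 8 to 14, "parasite prevalence was on average 25.8% but ranged from 0 to 71.4"%. For community surveys, it reports "parasite prevalences averaging 14.8% but ranging from 0% to 51.5"%. No standard deviation, number of community sites or number of people per site is given.

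On how hotspots are chosen, section 9c says that "no quantitative estimate of the elevated transmission intensity inside hotspots can be given a-priori since this depends on the transmission intensity of the surrounding area".

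**The concern.** Here k is the between-cluster standard deviation of true prevalence divided by its mean. A conservative value would err towards more variation. The protocol builds its rationale on striking heterogeneity between places, and its reported ranges are wide relative to their means. Yet it labels 0.5 cautious without showing why.

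The label matters because k dominates the zone calculation. If k is larger than 0.5, recruiting more people per cluster does little to restore power. A null result outside hotspots could then be read as absence of a community effect, when the trial had little chance of detecting the planned halving.

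**Working it through.** **Inputs.** Zone: p0 = 0.10, p1 = 0.05, m = 300. Hotspot: p0 = 0.20 (the protocol says above 20%), p1 = 0.05, m = 100. Both: k = 0.5 and 8 clusters per arm (16 in total). I assume that the printed 1.96 and 0.84 apply to both calculations, so (1.96 + 0.84)² = 7.84.

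**Formula** (standard unmatched cluster design, comparison of proportions):

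V = p0(1−p0)/m + p1(1−p1)/m + k²(p0² + p1²)

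c = 1 + 7.84 × V/(p0−p1)²

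power = Φ(√[(c−1)(p0−p1)²/V] − 1.96)

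**Zone figure at the protocol's own k.** Sampling part: 0.0900/300 + 0.0475/300 = 0.000458. Between-cluster part: 0.25 × (0.0100 + 0.0025) = 0.003125, which is 87% of V = 0.003583. Then c = 1 + 7.84 × 0.003583/0.0025 = 12.24, so 13 per arm, not 8. With 8 per arm, power = Φ(√(7 × 0.0025/0.003583) − 1.96) = Φ(0.25) = 60% (59% by a noncentral t with 14 df).

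The stated 8 was not reproduced by the variants tried with 300 people and 5% as the target: leaving out the added cluster gives 11.2, a one-sided test 9.9, and both together 8.9. Eight per arm reach 80% only if k is about 0.38 or less. At the protocol's limits of 100 and 500 people per zone, power at k = 0.5 is 50% and 62%. At k = 0.5 and m = 300, a fall to 4% needs c = 8.25 and a fall to 3.5% needs 6.97, so the smallest detectable reduction with 8 per arm is to slightly under 4%.

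**Hotspot figure.** V = 0.002075 + 0.25 × 0.0425 = 0.0127, so c = 1 + 7.84 × 0.0127/0.0225 = 5.43, or 6 per arm. The statement is supported at k = 0.5.

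**Effect of k with 8 clusters per arm:**

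| k | Zone: c needed | Zone: power | Hotspot: c needed | Hotspot: power |
|---|---|---|---|---|
| 0.50 | 12.2 | 60% | 5.4 | 94% |
| 0.55 | 14.3 | 53% | 6.2 | 90% |
| 0.60 | 16.5 | 47% | 7.1 | 85% |
| 0.65 | 19.0 | 42% | 8.0 | 80% |
| 0.70 | 21.6 | 37% | 9.0 | 75% |
| 0.80 | 27.5 | 30% | 11.2 | 64% |

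At the minimum of 50 people per hotspot, 80% power holds up to k of about 0.61.

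**What the reported spreads suggest.** The expected range of 46 normal values is about 4.4 SD. For the schools, SD ≈ 71.4/4.4 = 16.2 points and CV = 16.2/25.8 = 0.63. Subtracting binomial variance 0.258 × 0.742/n leaves about 0.55 with 30 children per school and 0.61 with 100 (both assumed). A beta model fitted to the largest of 46 values gives 0.64 to 0.68 for an assumed 20 to 100 children. Dividing the range by 6 gives 0.46, but that is a wide divisor for 46 units.

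For the community surveys, an assumed 20, 50 or 100 sites gives CVs of 0.93, 0.77 and 0.69 before sampling error. Net of it, the span is about 0.54 to 0.90 for 30 to 100 people per site.

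In a beta-binomial simulation of 46 schools at k = 0.5, the chance of seeing both a 0% school and one at or above 71.4% is about 19%, 9%, 3% and 0.4% with 20, 30, 50 and 100 children per school. At k = 0.7 it is about 63%, 51% and 29% with 30, 50 and 100.

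**The case against.** A reader might infer that the protocol's own data disprove k = 0.5. They do not, for four reasons.

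- **Different units.** The trial's k concerns true prevalence between evaluation zones (or hotspots) within an arm, inside one 5 × 20 km strip at 1400 to 1550 m. The ranges are observed extremes from schools and community sites across the district.
- **Selection.** A hotspot must show significantly higher parasite prevalence than its surroundings, so a place near 0% could hardly qualify. Removing the low end can narrow the spread: a beta distribution with mean 25.8% and k = 0.60, cut off below an assumed 5% or 10%, has k of 0.55 or 0.48. Because the criterion is relative to the surroundings, it does not make absolute prevalence alike across clusters. How far it narrows the spread between zones is unknown.
- **Unstated sample sizes.** With only 14 children per school, the observed school range would have about a 50% chance at k = 0.5.
- **Planned analysis.** Section 10b specifies stratified t-tests and adjustment for covariates, including baseline infection. These may reduce the effective between-cluster variation below the raw spread.

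All four stand against a claim of contradiction. None supplies a reason to call 0.5 conservative, and none explains how 8 per arm follows from the stated inputs.

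A second tempting inference is that the hotspot calculation loses its margin. At the 0.55 to 0.60 that the school range suggests, hotspot power is still 90% to 85%.

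**Conclusion.** The word conservative is unsupported. The reported spreads make k above 0.5 plausible without fixing it. The firmer result needs no outside k: at 0.5, 8 clusters per arm give about 60% power for the main comparison, against the 80% implied by the printed 0.84. Each further rise in k costs more, to 47% at 0.6 and 37% at 0.7. The hotspot statement is sound at k = 0.5 and fails only above about 0.65.

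This rests on the unmatched formula without stratification or covariate adjustment, on the printed error rates applying to both calculations, and on 20% as the starting prevalence in hotspots. The values of k inferred from the ranges also rest on assumed numbers of sites and of people per site.

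**What to change.** In section 9e:

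1. Delete the word conservative.
2. Before randomisation, estimate k separately for the hotspots and for the 500 m zones from the PCR results of the survey of about 3,200 compounds already done in the study area, subtracting binomial sampling variance.
3. For both calculations, restate the power or the smallest detectable reduction with 8 clusters per arm, at that k and at its upper confidence limit. If the survey estimate cannot be used, show the figures over k = 0.5 to 0.8.
4. Give the correct zone figure at k = 0.5 (13 per arm, or about 60% power with 8), and state the significance level and power beside it.

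The cost is a short calculation on existing data and a rewording, with no extra participants. The downside is a less favourable stated power.

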**9. DESIGN AND METHODOLOGY:**

## a. General study design

This study is a cluster-randomized trial where we compare the impact of hotspot targeted interventions on malaria transmission. Up to 16 clusters will be defined based on currently ongoing activities with half receiving the interventions. In each of the intervention clusters, all 4 hotspot-targeted interventions will be superimposed on ongoing control measures: hotspots will be targeted with a combination IRS, LLINs, larviciding and FSAT. The other clusters will serve as controls; these areas will not be targeted.

The interventions will be evaluated in the context of ongoing malaria control efforts. In the entire study area current ongoing malaria control interventions will continue without interruption.

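### Eight clusters per arm does not follow from the stated inputs: 10% versus 5% with 300 people per cluster and k = 0.5 needs 13 per arm, and 8 gives about 60% power

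*Protocol*

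**What the plan says.** Section 9e (Sampling strategy and sample size calculation) makes the area around the hotspot the target: "Our primary outcome of interest is the impact of hotspot-targeted interventions on parasite prevalence in the area surrounding the hotspot (the evaluation zone"). It then gives the inputs:

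- Sample per cluster: "If we evaluate our intervention in 300 randomly selected individuals living outside the hotspot per cluster". The actual number may vary, with "or a minimum of 100 and maximum of 500 people".
- Between-cluster variation: "assume a conservative estimate of k (0.5 coefficient of variation of true proportions between clusters within each group").
- Conclusion: "we need 8 clusters per arm to detect a reduction from 10% parasite prevalence at baseline to ≤ 5% after the intervention".

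That sentence states no significance level or power. The in-hotspot calculation later in the section gives k = 0.5, a two-sided z of 1.96 and a power z of 0.84.

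Section 9a sets 8 per arm as a ceiling: "Up to 16 clusters will be defined based on currently ongoing activities", half of them receiving the interventions. Section 10b cites a cluster-trial sample-size paper (reference 30) for its methods and plans unpaired t-tests, with stratification.

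Section 9e also converts people to compounds twice. For the evaluation zone, "therefore 100 people would equate to approximately 35 compounds". For the hotspots it sets "a minimum of 50 individuals (approximately 9 compounds").

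**The concern.** The evaluation-zone comparison is the trial's main question, and the sample-size sentence is its only statement of what the trial can detect there. With k = 0.5, between-cluster variation is by far the largest part of the variance, and eight clusters per arm looks too few to separate 10% from 5%.

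If so, the protocol claims a sensitivity that the stated calculation does not support. A real halving of prevalence around the hotspots would be missed about four times in ten, and the null result could be read as evidence that hotspot targeting has no community effect.

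**Working it through.** **Inputs.** p0 = 0.10, p1 = 0.05 (the boundary of the stated range), n = 300, k = 0.5 in each arm and c = 8 all come from the evaluation-zone sentence in Section 9e. The values z = 1.96 and 0.84 are printed in the same section for the hotspot calculation. Carrying them over is an assumption.

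**Formula** (unmatched clusters, k in each arm):

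c = 1 + (z_α/2 + z_β)² × [p0(1−p0)/n + p1(1−p1)/n + k²(p0² + p1²)] / (p0 − p1)²

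**Attempt to reproduce 8.**

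- Variance term: 0.09/300 + 0.0475/300 + 0.25 × (0.01 + 0.0025) = 0.000300 + 0.000158 + 0.003125 = 0.003583.
- (1.96 + 0.84)² = 7.84 and (0.10 − 0.05)² = 0.0025.
- c = 1 + 7.84 × 0.003583/0.0025 = 12.24, so **13 per arm**. The stated 8 is not reproduced.

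**Power at 8 per arm.** Φ(√(7 × 0.0025/0.003583) − 1.96) = Φ(2.210 − 1.96) = **59.9%**. A noncentral t with 14 degrees of freedom gives 59.4%. A beta-binomial simulation gives 61% on raw proportions and 58% on the log scale. At 13 per arm the formula gives 82.5%.

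**Does another convention give 8?**

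| Variant | c | Per arm |
|---|---|---|
| Without the +1 | 11.24 | 12 |
| Matched (+2) | 13.24 | 14 |
| One-sided 5% | 9.85 | 10 |
| One-sided 5%, without the +1 | 8.85 | 9 |
| Log scale | 10.68 | 11 |
| 90% power | 16.06 | 17 |
| n = 500 (stated maximum) | 11.66 | 12 |
| n = 100 (stated minimum) | 15.11 | 16 |
| Unlimited n | 10.80 | 11 |

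The only route found to 8 is a design effect without the +1 that applies the 5% arm's intracluster correlation to both arms: ICC = 0.25 × 0.05/0.95 = 0.0132; design effect 1 + 299 × 0.0132 = 4.93; 435 × 4.93/300 = 7.15, so 8. It gives the control arm less variation than the stated k. With the 10% arm's correlation (0.25 × 0.10/0.90 = 0.0278) the same route gives 13.49, so 14.

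**What would make 8 correct.** Changing one input and holding the rest:

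- k = 0.377 (0.409 without the +1), or
- p1 = 3.9% (4.2% without the +1).

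**Sensitivity at 10% versus 5%.**

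- 8 per arm, n = 100: variance term 0.0045; Φ(√(7 × 0.0025/0.0045) − 1.96) = 50%.
- 8 per arm, n = 500: 62%.
- 6 per arm, n = 300 (assumed, to show a shortfall below the ceiling of 16): Φ(√(5 × 0.0025/0.003583) − 1.96) = 46%.
- 8 per arm, n = 300, k = 0.6 (assumed): 47%.

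**Check on the companion calculation.** Inside hotspots, 20% to 5% with n = 100 and k = 0.5: variance term 0.0016 + 0.000475 + 0.25 × 0.0425 = 0.0127; c = 1 + 7.84 × 0.0127/0.0225 = 5.43, so 6. Eight per arm suffices (94% power). The error is confined to the evaluation zone.

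**Compound conversions.** 100/35 = 2.9 people per compound; 50/9 = 5.6. At 2.9, nine compounds yield 9 × 2.86 = about 26 people, roughly half the stated minimum of 50.

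**The case against.** The arithmetic is not in serious dispute, but several points bear on how far it reaches.

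- **No alpha or power is attached to the sentence.** True. The z-values are borrowed from the neighbouring calculation. They are the only ones given, and one-sided testing still needs more than 8.
- **The target is 5% or lower.** Larger falls are within the wording, and the simulation in Section 9e predicts a far bigger one (15% to below 0.1% overall). At 8 per arm, power is about 91% for 10% to 3% and 97% for 10% to 2%. So 60% is the power at the 5% boundary, not for every plausible effect. But the sentence includes that boundary, and there the claim fails.
- **Stratification and adjustment for baseline infection (Section 10b) may cut between-cluster variation.** They may. The gain cannot be determined from the protocol, and neither is an input to the stated figure.
- **The two compound figures describe different places**, and the provision that some age groups may not be sampled could change people per compound. That could explain the difference, but the protocol does not say so. The discrepancy is minor and does not enter the cluster calculation.

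These points limit the claim about the trial's eventual power. They do not rescue the sentence.

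**Conclusion.** The concern holds. On the protocol's own prevalences, sample per cluster and k, and assuming two-sided 5% and 80% power for an unadjusted comparison, the design needs 13 clusters per arm. Eight gives about 60% power for 10% versus 5%. The effect detectable at 80% power is a fall from 10% to about 3.9%. The shortfall of five clusters per arm cannot be made up by sampling more people, and it grows if zones are sampled at the 100-person minimum or if fewer than 16 clusters are found. Because this is the stated basis of the sample size for the main outcome, it must be corrected.

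**What to change.** Restate the evaluation-zone calculation in Section 9e:

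1. Give the significance level, sidedness and power explicitly.
2. State that with 8 clusters per arm, 300 people per cluster and k = 0.5, power for 10% versus 5% is about 60%, that the fall detectable at 80% power is to about 3.9%, and that 13 per arm would be needed for 5%. Alternatively, justify k of about 0.38 from the intensive baseline survey. Section 9e suggests its PCR results may still be pending, so this may have to wait for them.
3. Drop the description of k as conservative unless those data support it.
4. Add power for fewer than 16 clusters and for the 100-person minimum (about 50% with 8 per arm).
5. Use one people-per-compound figure in both conversions, or explain why they differ.

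The cost is protocol wording and a less favourable stated detectable effect. No extra clusters are required.

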**3. ABSTRACT:**

The burden of malaria is not equally distributed in Kenya. Some villages experience a higher exposure to malaria compared to neighbouring villages and even within villages some households are disproportionally affected. In the Rachuonyo district in the Kenyan highlands, this heterogeneity in malaria exposure is striking with parasite prevalence rates at schools ranging from 0% to >70%. The persistence of malaria in small geographical areas despite high coverage with insecticide treated nets (ITNs) and indoor residual spraying (IRS) may be partially explained by outdoor biting and resting of malaria vectors.

These insights in the micro-epidemiology of malaria transmission in Rachuonyo district suggest that a revision of malaria control strategies may be needed to successfully control and eliminate malaria. In the current study, we propose to determine the value of rolling out four targeted malaria control efforts simultaneously in reducing malaria transmission. These targeted control efforts include local upscaling of currently used IRS and ITNs in hotspots of malaria transmission. In addition, larviciding will be employed to target malaria vectors, also those that are less susceptible to IRS and ITNs as a consequence of outdoor feeding and resting. Lastly, the human infectious reservoir will be reduced by treating parasite carriers and their household members in hotspots of malaria transmission.

The impact of these targeted interventions will be assessed in the context of currently ongoing malaria control activities in a 2-year cluster randomized trial. In the cluster randomized trial up to 8 interventions clusters will be randomized to receive hotspot targeted interventions and compared with an equal number of control clusters where the (untargeted) malaria control activities continue. The intervention will be evaluated based on changes in parasite prevalence measured in community surveys inside and outside hotspots of malaria transmission.

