**6. Justification OF THE INTERVENTION:**

Seasonal indoor residual spraying with insecticides and campaigns to increase bednet coverage in the highlands of Western Kenya have reduced the burden of malaria in Rachuonyo district. However, the impact of the interventions is variable across the district and several areas continue to have high parasite prevalence rates among the general population and particularly among school children. These observations indicate that the current control efforts are insufficient to control or eliminate malaria in the area and additional efforts are needed.

For a maximum impact, these additional interventions should specifically aim to reduce malaria where it is most prevalent, target both indoor and outdoor biting and resting mosquitoes and also reduce the human infectious reservoir [[14](#_ENREF_14)]. When targeted to hotspots of malaria transmission, these interventions are expected to be highly efficacious in reducing malaria transmission locally and throughout the district.

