**Routine malaria control efforts in eight control clusters**

Any currently planned distributions of LLINs and yearly rounds of IRS will continue in the rest of the area. No interventions will be withheld from the population but no hotspot-targeted interventions will take place in the control clusters.

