## e. Sampling strategy and sample size calculation

The hotspot-targeted intervention will be evaluated inside and outside hotspots of malaria transmission. The latter is the main outcome measure of interest and forms the basis of sample size calculations. All available malaria simulation models indicate that malaria transmission in the area surrounding intervention hotspots would be considerably decreased because malaria transmission is effectively reduced/interrupted in those compounds that seed transmission to a larger geographical area [7-8, 19]. Because there are no published studies on the impact of hotspot targeted interventions, we determined the predicted impact of targeted interventions in our study area by one of the leading individual-based simulation model [19] using human, entomological and parasitological characteristics collected at our sites in Kenya. A previous study on the community benefits of insecticide treated nets in Asembo Bay, western Kenya, indicated that an indirect beneficial effect on malaria transmission may be limited to 500m from the intervention area [20]. We used this finding to define our evaluation zone surrounding the hotspots.

| [figure not shown] |
| --- |

***Figure 3. The predicted impact of untargeted and targeted interventions predicted by an individual-based simulation model.*** *Plotted are smoothed lines, the actual model estimates allow for seasonality.*

We modelled three scenarios in situations with a pre-intervention parasite prevalence in the human population of 5-15%: i) indoor residual spraying (IRS) in an untargeted approach, reaching 20% of the total population (black top line); ii) effective coverage with long lasting insecticide treated nets (LLINs) in an untargeted approach, reaching 80% of the total population (middle dashed grey line); iii) targeted IRS and 95% effective coverage with LLINs in the hotspots (bottom light grey line). The impact of larviciding is currently insufficiently parameterized to be included in the model [19].

We assumed a conservative estimate of the efficacy in detecting hotspots (75%, compared to 93% in Tanzania [[3](#_ENREF_3)]). Our simulations showed that targeted interventions can interrupt transmission completely, both inside and outside hotspots of malaria transmission, reducing overall parasite prevalence from 15% to <0.1%, in a manner that appears sustainable in the following years (see figure 3).

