**10. DATA MANAGEMENT:**

a. Data storage

All data from the questionnaires during cross-sectional surveys will be collected on PDAs and downloaded each evening into Microsoft Access. Paper records will be used as a back-up to the PDAs for recording visited households and RDT and anaemia results. All consents, assents, PDAs and computers to which data are downloaded will be locked so that only the principal investigators and data management staff will have access to the data. Data will be cleaned on an on-going basis.

b. Data analysis

To assess the impact of the intervention, methods appropriate for cluster-randomized trials will be used [30]. The primary outcome will be PCR-confirmed parasitaemia. The prevalence by PCR in each cluster will be calculated and the unadjusted risk ratio (RR), or mean difference between clusters will be calculated. An overall estimate of programme impact will be obtained, and 95% confidence intervals will be adjusted for observed between-cluster variance. Formal hypothesis testing will be undertaken using stratified unpaired t-tests. Adjustment for covariates will be undertaken replacing the cluster means and proportions with covariate-adjusted residuals from regression analysis of individual-level data.

One of the key outcomes of the study is the community-wide effect of hotspot targeted interventions. To address the question of the distance over which this community-wide effect exists, we will relate parasite prevalence and antibody prevalence to the distance from the centre of the hotspot in intervention and control clusters.

Additionally, the analysis adjusts for baseline characteristics on malaria infection, haemoglobin concentration and socio-economic status. Statistical analysis will be carried out using STATA^®^ software, version 10.0. (Stata Corporation, Texas, USA).

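### The zone sample size uses baseline prevalence as the control-arm value without saying so, and even at that value 8 clusters per arm give about 59% power, not 80%

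*Protocol*

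**What the plan says.** Protocol section 9e makes the zone around the hotspots the basis of the sample size. It starts from "If we evaluate our intervention in 300 randomly selected individuals living outside the hotspot per cluster", takes k = 0.5 between clusters within each group, and concludes that 8 clusters per arm are needed "to detect a reduction from 10% parasite prevalence at baseline" to 5% or less afterwards.

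The hotspot statement in the same section starts from an estimated prevalence above 20%, takes 100 people per hotspot in 16 clusters, and claims a detectable reduction to 5% or less. It prints k = 0.5, 1.96 and 0.84. The zone sentence prints no alpha or power.

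Section 10b calculates a risk ratio or mean difference between clusters, and "Formal hypothesis testing will be undertaken using stratified unpaired t-tests". On the control clusters, section 9d says: "Any currently planned distributions of LLINs and yearly rounds of IRS will continue in the rest of the area". Section 6 says that spraying and "campaigns to increase bednet coverage in the highlands of Western Kenya have reduced the burden of malaria in Rachuonyo district". The surveys in section 9g fall in March, June and September of two years, with March as the pre-transmission baseline. No section gives an assumed control-arm prevalence at any follow-up survey.

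**The concern.** For an unpaired comparison of arms, the first prevalence in the calculation must be that of the control arm at the survey being compared. The zone sentence supplies a baseline value instead. The two are the same only if control clusters do not change between baseline and that survey. The protocol neither states nor defends this, and its own text gives reasons to expect movement: continuing routine control and surveys in different seasons.

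At stake is the figure on which the trial's main question rests. If the sentence overstates what 8 clusters per arm can show, a null result outside the hotspots will look more informative than it is.

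**Working it through.** **Inputs** (section 9e): zone p0 = 0.10, p1 = 0.05, n = 300 per cluster, k = 0.5, 8 clusters per arm. Two-sided 5% and 80% power (1.96 and 0.84) are printed only with the hotspot statement; I assume they apply to the zone too.

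**Formula.** Section 10b cites a paper on sample size for cluster-randomized trials. The usual unmatched formula is

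c = 1 + (1.96 + 0.84)² × V / (p0 − p1)², with V = p0(1 − p0)/n + p1(1 − p1)/n + k²(p0² + p1²).

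**Zone: trying to reproduce 8.**
- V = 0.09/300 + 0.0475/300 + 0.25 × (0.01 + 0.0025) = 0.000300 + 0.000158 + 0.003125 = 0.003583.
- c = 1 + 7.84 × 0.003583/0.0025 = 1 + 11.24 = 12.24, so 13 per arm.
- Without the added 1: 11.24 (12). One-sided: 9.85 (10), or 8.85 (9) without the 1. Matched form: 13.24 (14). With n = 500: 11.66 (12).

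None of these variants gives 8. Eight per arm would follow from k of about 0.38, or from a fall to about 3.9% rather than 5%.

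**Power with 8 per arm at 10% versus 5%.** SE = √(0.003583/8) = 0.02116; 0.05/0.02116 = 2.36; noncentral t with 14 degrees of freedom gives 0.59. The normal form of the same formula gives 0.60. Section 9e allows 100 to 500 people per zone; over that range power is 0.50 to 0.62, so cluster size does not close the gap.

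**Dependence on control prevalence at follow-up** (assumed values; 8 per arm, n = 300, k = 0.5, noncentral t):

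| Control prevalence | Power, 50% relative reduction | Power, intervention fixed at 5% |
|---|---|---|
| 6% | 0.56 | 0.09 |
| 7% | 0.57 | 0.20 |
| 8% | 0.58 | 0.34 |
| 9% | 0.59 | 0.48 |
| 10% | 0.59 | 0.59 |
| 12% | 0.60 | 0.76 |

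The right-hand column does not isolate background change. At 7% versus 5% the relative reduction is (7 − 5)/7 = 29%, against 50% in the plan.

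**Hotspots** (n = 100, k = 0.5, intervention at 5%).
- V at 20% = 0.0016 + 0.000475 + 0.25 × (0.04 + 0.0025) = 0.0127.
- c = 1 + 7.84 × 0.0127/0.0225 = 5.43, so 6 per arm. Eight per arm is enough.
- Power with 8 per arm by control prevalence: 0.94 at 20%, 0.87 at 16%, 0.80 at 14%, 0.68 at 12%.

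**The case against.** The strongest reply is that the calculation is already a two-arm one. It speaks of clusters per arm and of k within each group, and section 10b defines impact between clusters. This stands: the fault is an unstated assumption about the control arm, not a before-after design. The words on baseline also occur only in the zone sentence; the hotspot sentence starts from an estimated prevalence.

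A reader might infer that continuing control would by itself cut power to 20-34%. The documents do not support that. Sections 9a and 9d superimpose the interventions on routine control that continues in the whole area, so a background decline would act on both arms. Those low figures hold the intervention arm at 5% and so assume a weaker intervention. With a constant relative effect, power hardly moves. The modelled net scenario, "in an untargeted approach, reaching 80% of the total population", is a simulation run and not a forecast for the control clusters.

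Nor is the direction settled. Routine nets and spraying were in place before baseline, baseline precedes the season while June is its peak, and the 2010 community average was 14.8%. Control prevalence could rise.

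A reader might also take the abstract's "The intervention will be evaluated based on changes in parasite prevalence measured in community surveys" to mean that success is reaching 5%. Section 10b rules this out, and nothing in the protocol defines success that way.

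None of this touches the cluster count, which fails even when control prevalence is exactly 10%.

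**Conclusion.** The point holds in two parts. First, section 9e uses the 10% baseline value as the control-arm prevalence for a between-arm test and so silently assumes no change in the control clusters. This is a gap in the stated assumptions; under a constant 50% relative reduction it costs little (power 0.56 to 0.60 for control prevalence of 6-12%). Second, and larger, 8 clusters per arm do not follow from the stated inputs: power is about 59%, and 13 per arm are needed for 80%.

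The hotspot statement is sound if 20% is the concurrent control prevalence, and it tolerates a fall to about 14%.

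The conclusions rest on k = 0.5 in both arms, 300 people per zone and 100 per hotspot, and the printed alpha and power applying to the zone. With k = 0.377, 8 per arm would give about 79% power in the zone, but the protocol states 0.5.

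**What to change.** In section 9e:

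1. State the zone target as control versus intervention prevalence at a named survey, for example a 50% relative reduction, and give the assumed control prevalence with its reason.
2. Replace the claim for 8 clusters per arm with about 56-60% power for that reduction over control prevalence of 6-12% (n = 300, k = 0.5, two-sided 5%), in a small table. Note that 80% power at 10% versus 5% would need 13 per arm.
3. For hotspots, state that 20% is the assumed concurrent control prevalence and that power stays at about 80% or more down to 14% with the intervention arm at 5%.

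The cost is one reworded paragraph and a table, with no added clusters or participants. The downside is that the trial's stated capability for its main question becomes less favourable.
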